### Sample size calculation

The primary objective is to determine the pCR rate in this trial. According to the results of the prospective phase II trial previously conducted at our center [20], the pCR rate of patients who received NCT was 14% (P0). We assume that after NCRT and six cycles of NCCT, the pCR rate will reach 28% in this study. Taking into consideration the loss of patients and the optimal two-stage design of phase II clinical trials, the test level α is 0.05 with a power of 80%. The required sample size of the study will be 82 patients. After 33 patients are enrolled, a planning interim analysis will be conducted. If the number of patients who received pCR is less than five, the study will be closed.

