### Statistical analysis

For descriptive statistics, categorical variables are described by frequency, rate, or 95% confidence interval. Continuous variables are described by the mean, median, quartile or standard deviation. For comparisons between groups, categorical variables will be compared by using the chi-square test or Fisher’s exact test. For continuous variables, the paired *t* test or Wilcoxon test will be used to compare changes between baseline and endpoint. The Kaplan–Meier method will be used to predict overall survival probabilities at specific time points. All statistical tests will be two-sided. The level of significance will be set to *P* < 0.05.

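### The interim rule closes the trial one pCR lower than the optimal two-stage design that the sizes 33 and 82 define, and the stated 80% power and loss allowance do not fit that design either

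*Protocol article*

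**What the plan says.** Everything that fixes the design is in the protocol article, Methods, Sample size calculation.

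- The null pCR rate P0 is 14%, taken from the centre's own earlier trial. The assumption for the new regimen is that "the pCR rate will reach 28% in this study".
- The design is described as "the optimal two-stage design of phase II clinical trials", introduced by "Taking into consideration the loss of patients". No loss rate is given.
- The error rates are given as "the test level α is 0.05 with a power of 80" per cent. This section does not say whether α is one-sided or two-sided. The Statistical analysis section says generally: "All statistical tests will be two-sided".
- The total is 82 patients. On the interim: "After 33 patients are enrolled, a planning interim analysis will be conducted". The rule is: "If the number of patients who received pCR is less than five, the study will be closed".

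In counts, the trial closes at 0 to 4 pCRs among 33 and continues at 5 or more. The article does not state how many pCRs among 82 would count as success.

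**The concern.** An optimal two-stage design is a fixed set of four numbers: first-stage size, first-stage boundary, total size and final boundary. They are chosen together to minimise expected enrolment when the regimen is no better than the null. If the two sizes come from one such design and the boundary does not, the operating characteristics are no longer those of the design named.

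Here the difference falls on the outcome of exactly 5 pCRs in 33. That is an observed rate of 15.2% (5/33), just above the 14% null and far from 28%. The design belonging to 33 and 82 closes there; the protocol goes on to enrol up to 49 more patients. At stake are the chance of stopping early for an ineffective regimen, the number of patients treated before that is known and, depending on the final cut-off, the type I error.

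**Working it through.** **Inputs** (Sample size calculation): p0 = 0.14, p1 = 0.28, α = 0.05, power 0.80, n1 = 33, N = 82, written boundary r1 = 4 (close at 4 or fewer). I take the optimal two-stage design to be Simon's, which is one-sided by construction.

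**Formulas.** With X ~ Bin(n1, p) in stage 1 and Y ~ Bin(N − n1, p) in stage 2:

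- P(stop | p) = P(X ≤ r1)
- P(success | p) = Σ over x > r1 of P(X = x) · P(Y ≥ c − x), where c is the number of pCRs needed among N. This is α at p0 and power at p1.
- Expected N at p0 = n1 + (1 − P(stop | p0)) · (N − n1)

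**Step 1: reproduce the stated sizes.** An exact-binomial search for the smallest expected N at p0 gives:

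| One-sided α, power | Design | Close at | Success at | α | Power |
|---|---|---|---|---|---|
| 0.05, 80%, optimal | 20 then 65 | ≤ 3 | ≥ 14 | 0.0476 | 0.803 |
| 0.05, 80%, minimax | 35 then 51 | ≤ 5 | ≥ 12 | 0.0453 | 0.801 |
| 0.025, 80%, optimal | 25 then 76 | ≤ 4 | ≥ 17 | 0.0250 | 0.808 |
| 0.05, 90%, optimal | **33 then 82** | **≤ 5** | **≥ 17** | 0.0498 | 0.901 |

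The stated inputs with 80% power do not give 33/82. With 90% power both sizes come out exactly, and the boundary is five or fewer.

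**Step 2: can loss inflation of the 80% design explain 33/82?** The article gives no loss rate, so assume 20%. Then 65/0.80 = 81.25, rounded up to 82, but 20/0.80 = 25, not 33. Inflation can explain the total but not the pair. If 82 is the 90% design as it stands, it contains no allowance for loss.

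**Step 3: the boundary, for n1 = 33 and N = 82.**

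- P(X ≤ 5 | 0.14) = 0.6878 and P(X ≤ 4 | 0.14) = 0.5008. The difference is P(X = 5 | 0.14) = 0.1870.
- Share of the stopping probability lost: 0.1870 / 0.6878 = 27%.
- Expected N at 14%, closing at ≤ 5: 33 + (1 − 0.6878) × 49 = 48.3.
- Expected N at 14%, closing at ≤ 4: 33 + (1 − 0.5008) × 49 = 57.5. The difference is 9.2 patients.
- Wrongly stopping at a true 28%: 0.068 with ≤ 5, 0.026 with ≤ 4.

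None of these figures depends on the final cut-off.

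**Step 4: type I error and power, which do depend on it.**

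| Close at | Success at | α | Power |
|---|---|---|---|
| ≤ 5 of 33 | ≥ 17 of 82 | 0.0498 | 0.901 |
| ≤ 4 of 33 (as written) | ≥ 17 of 82 | 0.0563 | 0.932 |
| ≤ 4 of 33 (as written) | ≥ 18 of 82 | 0.0316 | 0.901 |
| ≤ 4 of 33 (as written) | ≥ 19 of 82 | 0.0166 | 0.855 |

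**The case against.** The best defence is that the written rule can satisfy every error rate the article promises. Closing at four or fewer with success at 18 or more of 82 gives α 0.032 and power 0.901. Requiring 19 or more gives 0.0166 and 0.855, which would even fit a two-sided 5% level read as 0.025 per side. The looser rule also lowers the risk of abandoning a regimen that truly reaches 28%, from 6.8% to 2.6%. On this view only efficiency is lost.

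Much of this stands, and it rules out two stronger readings. A reader might infer that the written boundary breaks the 5% error rate. The article does not support that, because it states no final cut-off and a full protocol or SAP may fix one at 18 or higher. A reader might also infer that most of the early-stopping protection is gone. It is not: 0.501 of 0.688, about 73%, remains.

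Nor does the article show how the mismatch arose. A boundary of five that was turned into fewer than five is a likely explanation, given the exact match of both sizes, but it remains an inference.

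The defence does not rescue the claim of an optimal design. None of the combinations tried in the working gives 33, 82 and a boundary of four together.

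**Conclusion.** The concern holds in this form. The sizes 33 and 82 belong to the Simon optimal design for 14% against 28% at one-sided α 0.05 and 90% power, and the written interim boundary is one count below that design's. Whatever the final cut-off, the chance of closing at a true 14% drops from 69% to 50%, and about 9 more patients are expected to be enrolled under the null. The excess in type I error (0.0563) is conditional on success at 17 or more of 82.

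Two further statements in the same section do not fit: power of 80%, where 33/82 delivers about 90%, and a loss allowance that 82 does not contain.

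This rests on reading the optimal two-stage design as Simon's, on all 33 and all 82 patients being evaluable for pCR, and on a one-sided test. The last conflicts with the general two-sided statement in the Statistical analysis section. Under a strict 0.025 per side, 17 or more of 82 would not be enough with either boundary.

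**What to change.** Which correction applies depends on whether the interim has taken place; the article says only that recruitment is ongoing.

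- **Interim not yet run:** change the rule so that the study closes if five or fewer of the first 33 patients have a pCR, and state success as 17 or more of 82 (one-sided α 0.0498, power 0.901).
- **Interim already run under the written rule:** keep that rule and state success as 18 or more of 82 (α 0.032, power 0.901). Expected enrolment under the null then stays at 57.5.

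In either case, restate the power as about 90%, say that the primary test is one-sided and exempt it from the general two-sided statement, and correct the loss wording: either remove it, or add an allowance on top of 82 with its rate given.

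The cost is a short text correction. The boundary change needs no extra patients; an explicit loss allowance would. Closing at five or fewer raises the false-stop risk at a true 28% from 2.6% to 6.8%, which is already counted in the 90% power.

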### Statistical analysis

For descriptive statistics, categorical variables are described by frequency, rate, or 95% confidence interval. Continuous variables are described by the mean, median, quartile or standard deviation. For comparisons between groups, categorical variables will be compared by using the chi-square test or Fisher’s exact test. For continuous variables, the paired *t* test or Wilcoxon test will be used to compare changes between baseline and endpoint. The Kaplan–Meier method will be used to predict overall survival probabilities at specific time points. All statistical tests will be two-sided. The level of significance will be set to *P* < 0.05.

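### The rule that every test is two-sided conflicts with the one-directional two-stage design for pCR; with an exact test the verdict differs at 18 of 82

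*Protocol article*

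**What the plan says.** The Sample size calculation takes 14% as the null pCR rate and assumes that "the pCR rate will reach 28% in this study". The design is described as "the optimal two-stage design of phase II clinical trials, the test level α is 0.05", with 80% power. It adds that "The required sample size of the study will be 82 patients", with an interim look after 33 patients and closure if fewer than five have a pCR. It does not say whether alpha is one- or two-sided, and it gives no number of pCRs out of 82 that would count as success.

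The Statistical analysis section gives the general rule: "All statistical tests will be two-sided", with significance at P < 0.05. It makes no exception for the primary endpoint. The tests it names for categorical data are chi-square and Fisher's exact test for comparisons between groups, and this trial has one arm. For description, "categorical variables are described by frequency, rate, or 95% confidence interval".

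**The concern.** An optimal two-stage design works in one direction. It closes early for too few pCRs and rejects the null rate only for enough of them. A general rule that all tests are two-sided at 0.05 puts 0.025 rather than 0.05 in that direction. If it is applied to pCR, the final count needed is higher.

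The sponsor would then have two readings of the same result. In an open-label trial with no printed success count, the choice between them could be made after the count is known.

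**Working it through.** **Inputs.** From the Sample size calculation: p0 = 0.14, p1 = 0.28, alpha 0.05, power 0.80, n1 = 33, N = 82, close if fewer than five pCRs (r1 = 4, where r1 is the largest stage 1 count that closes the study). From the Statistical analysis section: two-sided, P < 0.05.

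**1. Which alpha gives 33 and 82?** An exact binomial search for the optimal design (smallest expected size under p0), written r1/n1, r/N with success if more than r pCRs:

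| One-sided alpha | Power | Optimal design |
|---|---|---|
| 0.05 | 80% | 3/20, 13/65 |
| 0.025 (two-sided 0.05) | 80% | 4/25, 16/76 |
| 0.05 | 90% | 5/33, 16/82 (alpha 0.0498, power 0.9006) |
| 0.025 (two-sided 0.05) | 90% | 7/41, 21/105 |

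Only one-sided 0.05 at 90% power gives both sizes. The stated 80% power does not.

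The section mentions loss of patients without a rate, so inflation was tried. The total can be reached: 65/(1 − 0.20) = 81.25, rounded up to 82; or 76/(1 − 0.07) = 81.7, rounded up to 82. The first stage cannot: 20/0.80 = 25 and 25/0.93 = 26.9, rounded up to 27, not 33. It is the 33 that points to the one-sided design. That design stops at five or fewer (r1 = 5), whereas the article prints fewer than five (r1 = 4), so both boundaries are carried forward.

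**2. One-sided two-stage rule.** The probability of success at rate p is the sum over x > r1 of P(X1 = x) × P(X2 > r − x), with X1 ~ Bin(33, p) and X2 ~ Bin(49, p). Alpha is its value at 0.14 and power its value at 0.28.

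| Success if | Printed rule (r1 = 4): alpha / power | Five or fewer (r1 = 5): alpha / power |
|---|---|---|
| ≥17 | 0.0563 / 0.9319 | 0.0498 / 0.9006 |
| ≥18 | 0.0316 / 0.9007 | 0.0287 / 0.8741 |
| ≥19 | 0.0166 / 0.8554 | 0.0154 / 0.8339 |

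The lowest count that keeps alpha at or below 0.05 is 18 with the printed rule and 17 with five or fewer.

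**3. Two-sided tests of 14% with n = 82.** For the normal test, z = (k/82 − 0.14)/√(0.14 × 0.86/82).

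| pCRs | Rate | Exact two-sided P | Exact 95% CI | z | Normal two-sided P |
|---|---|---|---|---|---|
| 17 | 20.7% | 0.081 | 12.6% to 31.1% | 1.757 | 0.079 |
| 18 | 22.0% | 0.054 | 13.6% to 32.5% | 2.075 | 0.038 |
| 19 | 23.2% | 0.024 | 14.6% to 33.8% | 2.393 | 0.017 |

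The exact test first succeeds at 19 and the normal test at 18. Doubling the one-sided two-stage alpha, which allows for the interim look, agrees with the exact test: at 18 it is 2 × 0.0316 = 0.063 (r1 = 4) or 2 × 0.0287 = 0.057 (r1 = 5); at 19 it is 0.033 or 0.031.

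**4. Disputed counts.** The probability at a true 28% is the difference between the powers in step 2.

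| Interim rule | Two-sided test | One-sided / two-sided cut-off | Disputed | Probability at 28% |
|---|---|---|---|---|
| Fewer than five (printed) | exact | 18 / 19 | 18 | 0.9007 − 0.8554 = 4.5% |
| Fewer than five (printed) | normal | 18 / 18 | none | 0 |
| Five or fewer | exact | 17 / 19 | 17, 18 | 0.9006 − 0.8339 = 6.7% |
| Five or fewer | normal | 17 / 18 | 17 | 0.9006 − 0.8741 = 2.7% |

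**The case against.** The best defence is that the contradiction is not printed. The article never calls the design one-sided, and it never applies a two-sided test to pCR against 14%. The two-sided sentence follows between-group tests, baseline-to-endpoint changes and Kaplan–Meier estimates, and may be meant only for those, with the two-stage rule deciding the primary endpoint. An article may also leave the one-sample test and the final count to a fuller document. The 95% confidence interval is listed under description and sets no decision rule.

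Most of this stands, and it limits the point. It does not remove it: the two-sided sentence has no exception, and an analysis plan written from it would carry it over to pCR.

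Two stronger readings are not supported. A reader might infer that 17 and 18 of 82 are both in dispute. That needs an interim boundary of five or fewer, which is not the printed one, together with an exact test. Under the printed rule 17 fails both ways, since success at 17 or more has alpha 0.056. A reader might also infer that a two-sided rule leaves the trial short of power. The only power the article states is 80%, and the strictest case here has 83.4%; the 90% comparator comes from reconstructing the design.

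**Conclusion.** The concern holds in a narrow form. The primary endpoint is sized with a one-directional rule whose stage sizes match a one-sided alpha of 0.05, and the general rule makes every test two-sided without exempting it.

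With an exact test, 18 of 82 is positive under one rule and negative under the other, whichever interim boundary is used. Under the printed boundary that is the only disputed count, with about 4.5% probability if the true rate is 28%. Across all readings the disputed set runs from no count to two counts. Among the rules that keep alpha at or below 0.05, power is 83.4% to 90.1%.

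This rests on the one-sidedness inferred from the match to 33 and 82, on all 82 patients being evaluable, and on the test chosen for the two-sided reading. That the disputed count moves with unstated choices is the reason to fix the criterion before the result is known.

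**What to change.** First reconcile the interim boundary: the article prints closure at fewer than five, while the design matching 33 and 82 closes at five or fewer.

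Then amend the Statistical analysis section to say that pCR is tested by the two-stage rule at one-sided alpha 0.05, and that all other tests are two-sided. State the final success count that keeps alpha at or below 0.05 for the boundary actually used:

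- at least 18 of 82 with the printed boundary (alpha 0.032, power 90.1%);
- at least 17 of 82 only if the boundary is changed to five or fewer (alpha 0.0498, power 90.1%). Pairing 17 with the printed boundary would give alpha 0.056, above the stated level.

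A two-stage-adjusted interval matching the one-sided level is optional.

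The cost is a few sentences in the protocol or analysis plan and no extra patients or data. It should be done before the primary result is known; the article reports recruitment as still ongoing.

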### Follow-up

After completing the treatment according to the protocol, patients will receive the examinations listed in Table 3. Patients will be examined every 3 months in the first 2 years, every 6 months during years 3 to 5, and then once a year after 5 years. During follow-up, investigators will collect information on surgical complications, late toxicity, other treatments, and recurrence and survival.

### Quality assurance

The quality assurance (QA) team associated with this study will include experienced experts in the field of radiotherapy, dosimetry, medical physics, medicine, surgery, imaging, pathology, and data censors. Diagnostic images before and after neoadjuvant treatment will be reviewed centrally and independently by two radiologists. The first three cases of target volume delineation from each center will be reviewed centrally and then checked randomly. Data censors in this study will stay in communication with branch-centers and check the quality of the data collection randomly.

### Data collection and management

Every center needs at least one physician to be responsible for enrolling patients in this trial and arranging patient therapy. Two physicians will collect data and complete the CRF at their center. When modifying data, the researcher will need to sign their name and record the date of modification on the CRF. The CRF will be regarded as raw material, and all data in the CRF will be archived electronically on a specific computer. All electronic documents will be confidential, and only the data manager will have the password. Only the project leader will have the right to use the database, and other researchers will not be allowed to use the database unless permitted.

## Discussion

GC ranks high in terms of morbidity worldwide, and multidisciplinary treatments are urgently needed, particularly for locally advanced GC. Recent published or ongoing clinical trials associated with NCRT or NCT are listed in Table 4. In our study, the objective will be to explore the short-term efficacy and safety of total neoadjuvant therapy for locally advanced GC and EGJ adenocarcinoma. The results may offer more therapeutic options for physicians to offer these patients.

**Table 4 Tab4:** Summary of published or ongoing prospective clinical trials associated with NCRT or NCT in EGJ/GC adenocarcinoma

Category	Author/year	No. of pts	Tumor stage	Study design	RT dose	Concurrent CT regime	CT regimes	Finding/ Clinical trial registration number
Neoadjuvant radiotherapy	Shapiro [7]	366	T2–3N0/N +	NCRT + S vs S	41.4 Gy	TC	/	7y OS: 41%vs28% (*P* < 0.05)
	Tian [21]	150	T2-4N0/N +	NCRT + S vs S	45 Gy	XELOX	/	3yOS:63.4% vs 52.2%(*P* = 0.019)
	Stahl [13]	126	cT3-4NxM0	NCT + NCRT + S vs NCT + S	30 Gy	EP	PF	5yOS:39.5% vs 24.4%(*P* = 0.055)
	Liu [22]	36	T4aN + /T4b	NCT + NCRT + S + CT	45 Gy	S-1	SOX	2y:56%
	Kim [23]	42	T3-4N0/N +	NCT + NCRT + S + CT	45 Gy	S-1	SOX	3y:75.5%
Perioperative chemotherapy	Cunningham [9]	503	T1-4N0/N +	NCT + S + CT vs S	/	/	ECF	5yOS:36.3%vs23% (*P* = 0.009)
	Ychou [10]	224	T1-4N0/N +	NCT + S + CT vs S	/	/	CF	5yOS: 38%vs24%(*P* = 0.02)
	Al-Batran [8]	716	T2-4N0/N +	NCT + S + CT vs NCT + S + CT	/	/	FLOT vs ECF/ECX	5yOS:45%vs36% (*P* = 0.012)
	Zhang [24]	1094	cT4aN + /cT4b	NCT + S + CT vs S + CT vs S + CT	/	/	SOX(Peri) vs SOX(post) vs XELOX(post)	3yDFS:59.4% vs 56.5% vs 51.1%(arm1 vs arm3:*P* = 0·028)
Ongoing	TOPGEAR [25]	752	T3-4N0/N +	NCT + NCRT + S + CT vs NCT + S + CT	45 Gy	5-Fu/Cap	ECF	NCT01924819
	PREACT [26]	682	T3-4aN + /T4b	NCT + NCRT + CT vs NCT + S + CT	45 Gy	S-1	SOX	NCT03013010
	NEO-CRAG	620	T3N2-N3/T4aN + /T4b	NCT + NCRT + S + CT vs NCT + S + CT	45 Gy	XELOX	XELOX	NCT01815853
	CRITICS II [27]	207	T2-4N0/N +	NCT + NCRT + S vs NCRT + S vs NCT + S	45 Gy	TC	DOC	NCT02931890
	CRADLE	214	T3-4N0/N +	NCRT + S + CT vs S + CT	50 Gy	SOX	SOX	NCT02193594

The CROSS study was the first to report a significant survival benefit for the NCRT group compared with the surgery alone group among patients with EGJ adenocarcinoma [7]. With the development of NCT, the choice between NCRT and NCT has become controversial. The POET study was the first to compare NCRT with NCT and found that NCRT significantly downstaged tumor stage and improved the pCR rate [13]. One meta-analysis confirmed that NCRT can improve local control compared with NCT, but improvements in overall survival were not observed [28].

Currently, the value of NCRT for EGJ is clearly verified and recommended by the NCCN guidelines [11]. However, the value of NCRT for middle and distal GC is still lack of reliable evidence. The RTOG9904 study included 42 patients with GC and firstly found the value of NCRT in GC. The pCR rate was 26%, and the 1-year OS was 72% in this study [29]. Recently, Liu et al. included 40 patients with GC who received NCRT. The pCR rate was 13.9% and the medial survival time was 30.3 months [22]. Ahmed et al. included 32 patients with GC who received NCRT. The pCR rate was 18.8% and the 2-year OS was 51.3% [30]. Although, some phase II clinical trial has found the value of NCRT in middle and distal GC, it still needs evidence from larger sample size prospective clinical trials.

Perioperative therapy has advanced rapidly, and 6–8 cycles of perioperative chemotherapy are currently recommended according to the NCCN guidelines [11]. In the MAGIC study, six cycles of an ECF/ECX (stepirubicin, cisplatin and fluorouracil or capecitabine) regimen were used before and after surgery; although overall survival improved, only 41.6% of the patients completed the planned six cycles [9]. In the FLOT4 study, only 46% of patients completed all perioperative treatments [8]. In the CRITICS trial, the completion rate of adjuvant chemotherapy and chemoradiotherapy was 60% [12]. As mentioned above, the complete percentage of adjuvant therapy was quite low. Hence, in this trial, all perioperative treatment was administered before surgery. Moreover, preoperative chemotherapy may reduce the surgery rate for potential distant metastasis patients. In recent years, an increasing number of investigators have focused on the use of a total neoadjuvant therapy modality in patients with gastrointestinal tumors, especially those with rectal cancer [31], yet similar studies on GC are quite limited. Kim et al. explored the induction of NCT followed by NCRT for GC patients; adjuvant chemotherapy was needed for patients whose tumors were not downstaged to stage 0 to I after surgery. A total of 42 patients were enrolled in their study; 33.3% were pathologically downstaged to stage 0-I after preoperative treatment, and the 3-year overall survival rate was 75.5% [23]. The results of the use of total neoadjuvant therapy approaches for GC and EGJ adenocarcinoma phase II clinical trials were published at the 2019 ASTRO (American Society for Therapeutic Radiology and Oncology) meeting. Patients received 8 cycles of induction chemotherapy (FOLFIRINOX: Oxaliplatin, Irinotecan, Fluorouracil and leucovorin) followed by NCRT and surgery. Of the 25 patients enrolled in this trial, 20 underwent surgery, and the pCR rate was 35%. The results of this trial demonstrated the promising effects of total neoadjuvant therapy [32]. To further improve the downstaging rate, we prolonged the interval time between radiotherapy and surgery. The strategy of receiving NCRT followed by NCCT and surgery is rarely reported for GC.

